## Abstract

**Background:**

A lifestyle including poor diet, physical inactivity, excessive gaming and inadequate sleep hygiene is frequently seen among Dutch children. These lifestyle behaviors can cause long-term health problems later in life. Unhealthy lifestyle and poor physical health are even more prevalent among children with mental illness (MI) such as autism, attention-deficit/hyperactivity disorder, depression, and anxiety. However, research on lifestyle interventions among children with MI is lacking. As a result, there are currently no guidelines, or treatment programs where children with MI and poor lifestyle can receive effective support. To address these issues and to provide insight into the effectiveness of lifestyle interventions in children with MI and their families, the Movementss study was designed. This paper describes the rationale, study design, and methods of an ongoing randomized controlled trial (RCT) comparing the short-term (12 weeks) and long-term (1 year) effects of a lifestyle intervention with care as usual (CAU) in children with MI and an unhealthy lifestyle.

**Methods:**

A total of 80 children (6–12 years) with MI according to DSM-V and an unhealthy lifestyle are randomized to the lifestyle intervention group or CAU at a specialized child and adolescent mental hospital. The primary outcome measure is quality of life measured with the KIDSCREEN. Secondary outcomes include emotional and behavior symptoms, lifestyle parameters regarding diet, physical activity, sleep, and screen time, cognitive assessment (intelligence and executive functions), physical measurements (e.g., BMI), parenting styles, and family functioning, prior beliefs, adherence, satisfaction, and cost-effectiveness. Assessments will take place at the start of the study (T0), after 12 weeks (T1), six months (T2), and 12 months of baseline (T3) to measure long-term effects.

**Discussion:**

This RCT will likely contribute to the currently lacking knowledge on lifestyle interventions in children with MI.

**Trial registration:**

trialsearch.who.int/ NL9822. Registered at November 2^nd^, 2021.

## Background

In recent years, increasing attention has been given to lifestyle and their effects on mental health. Various studies consistently show that adults with mental illness (MI) have higher rates of physical ill health and die earlier than those in the general population, largely due to treatable conditions associated with modifiable risk factors such as smoking, obesity, substance misuse, and adverse effects of medication [1, 2]. A recent meta-analysis shows promising effects of lifestyle interventions in adults with MI on their mental health [3].

Unhealthy lifestyle and poor physical health are also frequently seen among children with MI, such as autism spectrum disorders (ASD), Attention Deficit Hyperactivity Disorder (ADHD), depression, and anxiety disorders, compared to children without MI [4, 5]. An unhealthy lifestyle among children consists, for example, of low physical activity [6], poor nutrition intake [7], disrupted sleep [8, 9], and elevated screen time [5, 10]. An unhealthy lifestyle in the family may have a major impact on the mental, physical and social functioning of children [11]. However, longitudinal studies of lifestyle interventions in children with MI are relatively sparse [3].

Research on lifestyle-related factors and integrated lifestyle programs for children and their families in the general population is increasing [12, 13]. Nevertheless, children with MI are generally excluded from these integrated lifestyle programs because of the perceived complexity of care for these families. Therefore, data on lifestyle interventions for children with MI and their caregivers are sparse. Moreover, treatment expertise of an integrated approach to lifestyle factors in child mental health hospitals is lacking. A major concern is that children with MI are at high risk of developing chronic physical and mental health issues and, consequently, require lifelong healthcare services because of the complex interaction between unhealthy lifestyle, physical and mental comorbidities, and adverse effects of psychotropic medication at a young age [3]. The main lesson from other lifestyle interventions, such as those developed for obesity, is that the later the start of intervention for physical comorbidities, the poorer the outcomes at an older age [14]. From a preventive perspective, a multimodal lifestyle intervention program for children with MI is needed to improve mental and physical outcomes.

Based on the programs for children without MI, the Movementss study has been developed. This is a multi-modal lifestyle intervention program with a systematic approach focusing on four lifestyle parameters (i.e., movement/physical activity, nutrition intake, sleep behavior, and screen time restoration) for children with MI and their families. The trial will focus on the relationship between an integrated lifestyle intervention program and the quality of life for children with mental illness and their families. To assess the added value of this lifestyle intervention, children will be randomized into two groups: intervention and care as usual group. The intervention involves family-based education on a healthy lifestyle in combination with cognitive behavior therapy (CBT) for the child and psychomotor systematic therapy (PMST) for the whole family given by mental health professionals. In PMST, the child and caregiver work in a body-oriented manner, and they both learn concrete skills (i.e., an action-oriented approach) [15–17]. Also, during PMST, systemic interaction patterns between family members will be established. Furthermore, from integrated lifestyle intervention programs for children without mental illnesses, it is known that children need support from their families, and unhealthy lifestyle habits need to be targeted using a family-based intervention [18]. For this reason, caregivers and mental health professionals will actively participate in the intervention. To generalize healthy behavior in the family, a home coach will be involved to visit the child and family at their homes.

Since a healthy lifestyle contains multiple elements (i.e., nutrition, sleep, screen time, and physical activity), the intervention will have a tailored approach, where the child and caregiver will take the lead in their goal setting. An integrated approach focusing on multiple lifestyle factors (including psycho-education and skills training), social (peer)support, and guided by qualified professionals does have the best chance of success [19–21]. For lifestyle interventions to succeed, it is highly relevant that the focus on lifestyle factors and specific goals is tailored to the needs, interests, and environment of the participants [19]. Using goal setting in this integrated and tailor-made intervention allows for easier translation to daily life.

The primary objective of the Movementss study is to quantify the short-term (after 12 weeks) and long-term (after 6 and 12 months) effectiveness on quality of life compared to care as usual (CAU) in children aged 6–12 years with MI. We hypothesize that the lifestyle intervention will be more effective than CAU. The second aim is to examine the short- and long-term effects of the lifestyle intervention compared to CAU on outcome measures related to mental and physical symptoms and lifestyle problems such as emotional and behavioral problems, cognitive outcomes, sleeping, eating patterns, and weight status. It is hypothesized that lifestyle improvement will have a positive effect on these mental and physical symptoms. Additionally, the third aim is to investigate the cost-effectiveness of the lifestyle intervention compared with CAU. We assume that intervening in lifestyle at such a young age will result in less expensive care in the long term. Also, this study aims to identify potential moderators of adherence or responders to the treatment (e.g., SES, ethnicity, comorbidity). Finally, qualitative questions will be addressed in this study by examining the potential facilitators and barriers to the lifestyle intervention.

## Method

### Study design

This study uses a mixed-methods design combining a two-arm randomized controlled trial with semi-structured interviews to capture caregivers’ and professionals’ experiences before and after the lifestyle intervention, using repeated measures and semi-structured interviews. The aim of combining quantitative and qualitative components within this study is to provide a better understanding of the effectiveness of the lifestyle intervention.

### Quantitative study

#### Participants

The medical ethics Committee on Research involving Human Subjects of Radboudumc (CCMO, Arnhem-Nijmegen) approved the study and it is registered under 2021–8224. Written informed consent regarding participation and publication from all parents or guardians for participants under 16 years will be obtained during the randomized controlled trial.

Participants will be recruited among new referrals at Karakter Child- and Adolescent Psychiatry and Denkkracht, The Netherlands. Karakter is a hospital for specialist mental health care, and Denkkracht a center for neuropsychological expertise. The selection of participants is a 2-step process. First, our digital intake questionnaire is used to select potential participants. Before the first appointment at the clinic, parents must complete this digital intake questionnaire. This assessment includes age, sex, country of birth, and parents’ educational level. In the section on lifestyle, various questions about physical exercise, healthy eating behavior, sleeping patterns, and screen time are asked. Potential participants are selected when they positively respond to one or more of the following questions:How much time does your child spend in front of a screen compared to peers (*More* or *Much more*)How much exercise does your child have compared to peers? (*Less* or *Much less*)How often does it take longer than 30 min for your child to fall asleep? (*Always*)How often does your child wake up more than three times per night, or does your child lie awake for more than 20 min per night? (*Always*)How often does your child wake up before 6 am? (*Always*)How often does your child experience daytime fatigue? (*Always*)How many days a week does your child eat breakfast? (*(Almost) never* or *1–2 days a week*)How many days a week does your child eat fruit? (*(Almost) never* or *1–2 days a week*)How many days a week does your child eat vegetables? (*(Almost) never* or *1–2 days a week*)How many times a day does your child get snacks (biscuits, candy, chips)? (*5–6 times a day* or *More than seven times a day*)How many days a week does your child eat “fast food” (pizza, chips, pancakes, chip shop, snack bar, etc.)? (*5–6 days a week* or *Every day*)

Secondly, following a positive response to these items, participants are invited for a somatic assessment and eligibility check for the Movementss study by a nurse specialist and child and adolescent psychiatrist. Somatic assessment includes measurement of weight, height, blood pressure, heart rate, head circumstances, an inspection of dysmorphic features, and motor functioning and coordination.

For eligibility, participants must meet the following criteria: 1) 6–12 years old at the inclusion date, 2) DSM-5 diagnosis (any presentation), 3) somatic or lifestyle problems assessed by somatic examination and lifestyle screening (overweight, obesity, underweight, unhealthy diet, sleeping problems, inactivity, and screen time use), and 4) willingness to set lifestyle goals. Comorbidities are allowed except for eating disorders (i.e., anorexia or bulimia nervosa) and diabetes mellitus. Exclusion criteria are: 1) unable to respond to questions (parents or children), 2) no access to a home internet connection, 3) insufficient mastery of the Dutch language in parents or children, 4) physically incapable of doing physical exercises, 5) surgery in the past six months or next twelve months impacting physical activity or dietary intake, 6) any somatic condition severely restricting diet, current treatment for the psychiatric diagnosis, and 7) an intelligence quotient (IQ) below 70. Participants receiving this lifestyle intervention cannot start any other treatment during the 12-week-long lifestyle intervention, except for the optimization of pharmacotherapy. For children who receive medication, this will be optimized during the lifestyle intervention. During this optimization, the physical health of the children will be closely monitored since lifestyle-related problems (e.g. sleeping problems, reduced appetite, and overweight) more often occur when using medication. Similarly, participants receiving CAU will receive one session of digital psycho-education on a healthy lifestyle though they will not follow a lifestyle intervention.

#### Randomization

The Movementss study is a two-arm randomized controlled trial; patients fulfilling eligibility criteria and willing to participate will be randomized after baseline assessment (1:1 allocation ratio) in either the lifestyle intervention or CAU group using block randomization, with varying random block sizes of 2, 4 or 6. A priori, an independent statistician will prepare a computer-generated randomization schedule stratified for weight (underweight, normal, overweight), sex (male, female), and age (6–8 years, 9–12 years) to ensure that the number of participants in both treatment arms is closely balanced within each stratum. Castor EDC will be used for the actual randomization process. After obtaining informed consent and baseline measurements, the study coordinator will provide the randomization code. Participants, researchers, and practitioners are aware of treatment allocations.

#### Procedures

Families interested in participating in the Movementss study are informed by telephone and information letters (sent via e-mail). If the eligibility criteria are met, parents and children are invited for an intake consult (via e-health or at the psychiatry clinic), explaining further details of participating in the study. Both parents fill out written informed consent for the Movementss study (Additional file 1).

Assessments will take place at baseline (T0), after twelve weeks of treatment (T1), after six months from baseline (T2), and twelve months from baseline (T3) (i.e., lifestyle intervention with CAU). T0 will be scheduled three weeks before the start of the treatment. T0 and T1 will take place at Karakter Child and Youth Psychiatry. For the T2 and T3 assessments, parents are asked to fill out questionnaires online. Figure 1 describes a flowchart of recruitment and the procedure for the study. It is estimated that the study’s data collection will be completed in spring 2024 (*N* = 80), and the follow-up data will be completed at the beginning of 2025.

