Parallel to these sessions on location, the family will receive visits from the homecoach. The order of the sessions is the guideline for the intervention, however, a certain degree of flexibility is required and accepted in order to make the intervention fit to the family

*CBT* Cognitive Behavioral Therapy, *PMST* Psychomotor Systematic Therapy

^a^The Beweegrichtlijn 2017 advises children (4–18 years) to exercise moderately for at least an hour a day. Longer, more frequent, and/or more intensive exercise provides additional health benefits. Furthermore, children are advised to do muscle and bone-strengthening activities at least three times per week and to avoid a sedentary lifestyle

This intervention will be given by trained mental health professionals (i.e., psychologists and nursing specialists). Prior to the start of the intervention, these professionals received a three-day training by experts in the field focusing on sleep-promoting behavior, healthy eating behavior, screen time (addiction), and motivational interviewing.

The lifestyle intervention consists of a 12-week program (see Table 1) where the child and parents are treated intensively (approximately two hours a week). The intervention will start with psychoeducation sessions on a healthy lifestyle. In addition to providing more information about a healthy lifestyle, psychological treatment is necessary to achieve and maintain behavioral change. CBT has great evidence as an effective intervention method for behavioral change in mental health problems in adults and children (e.g., sleeping problems and eating disorders) [22]. Due to the amount of evidence of CBT, and the focus on both cognitions and behavior in lifestyle behavior, this psychological treatment was chosen for this intervention. A workbook is available for the child and the parents and contains information about a healthy lifestyle and describes the various assignments in detail. See Table 1 for a more detailed description of the content of the sessions. While the order of the sessions is the guideline of the intervention, a certain degree of flexibility is needed to fit the family's needs.

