### Outcomes

Outcome parameters and measurement times are assessed as shown in Table 2.

**Table 2 Tab2:** Outcome parameters from baseline to 12 months after baseline

Measurement	T0^a^	T1^b^	T2^c^	T3^d^	Instrument
*Descriptives*					
A. Descriptives	T0				Intake questionnaire
B. Psychiatric evaluation	T0				DSM-V
C. Intelligence quotient (IQ)	T0				WISC-V
*Primary outcome*					
D. Quality of life	T0	T1	T2	T3	Kidscreen-27
*Secondary outcomes*					
E. Emotional and behavior problems	T0	T1	T2	T3	CBCL
F. Cognitive performance	T0	T1			COTAPP
G. Somatic measurements	T0	T1		T3	Somatic screening
H. Blood laboratory tests	T0				Blood samples (15 ml) sober
*Lifestyle parameters*					
I. Sleep: Sleeping habits	T0	T1	T2	T3	CSHQ
J. Sleep: Sleeping dairy	T0	T1	T2	T3	Sleep–wake diary
K. Sleep: 24 h sleep/wake measurements	T0	T1	T2	T3	Actigraphy
L. Diet: Food consumption	T0	T1	T2	T3	Nutrition diary
M. Diet: Eating habits	T0	T1	T2	T3	Eating habits questionnaire
N. Physical activity: Physical fitness	T0	T1		T3	Shuttle run test
O. Physical activity: Physical activity	T0	T1	T2	T3	Physical activity questionnaire
K. Physical activity: Actigraphy	T0	T1	T2	T3	Actigraphy
P. Screen time: Screen activities	T0	T1	T2	T3	Screen time questionnaire
*Measurements of costs*					
Q. Used healthcare resources				T3	Tic-P questionnaire
*Other study parameters*					
R. Parenting styles	T0	T1	T2	T3	VSOG
S. Parenting functioning	T0	T1	T2	T3	VGFO
T. Prior beliefs	T0				5-item questionnaire
U. Patient satisfaction			T2	T3	GGZ-Jeugdthermometer

*DSM* Diagnostic and Statistical Manual of Mental Disorders, *WISC* Wechsler Intelligence Scale for Children, *IQ* Intelligence quotient, *CBCL* Child Behavior Checklist (6–18), *CSHQ* Children’s sleep habit questionnaire, *Tic-P* Trimbos and iMTA questionnaire on Cost associated with Psychiatric illness, *VSOG* Verkorte Schaal voor Ouderlijk Gedrag, *VGFO* Vragenlijst Gezinsfunctioneren Ouders

^a^T0 Baseline

^b^T1 twelve weeks after baseline

^c^T2 six months after baseline

^d^T3 twelve months after baseline

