#### Primary outcome

D. Quality of lifeParents are invited to rate the children’s quality of life using the KIDSCREEN-27 [26]. The KIDSCREEN-27 is a generic health-related quality of life (HRQOL) questionnaire for children and adolescents applicable for healthy and chronically ill children and adolescents aged between 8 and 18 years [26]. The KIDSCREEN-27 consists of 27 items that measure five dimensions: physical well-being, psychological well-being, parent relations & autonomy, social support & peers, and school environment. Items are answered on a five-point Likert-type scale assessing frequency: *never* (1), *seldom* (2), *sometimes* (3), *often* (4), and *always* (5), or intensity: *not at all* (1), *slightly* (2), *moderately* (3), *very* (4), and *extremely* (5), with a 1-week recall period. Scores are coded from 1 to 5, negatively formulated items will be recoded, and the sum scores for respective dimensions are transformed to* T* scores with a mean of 50 and a standard deviation (SD) of 10: higher scores indicate better HRQOL [26]. The KIDSCREEN-27 has been shown to have robust psychometric properties [26]. The internal consistency of the domains was between 0.81 and 0.84, and the test-retest reliability of the domains ranged from 0.61 to 0.74 [26]. Quality of life is assessed at T0 (Baseline), T1 (end of intervention), T2 (six months after baseline), and T3 (12 months after baseline).

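### Table 2 dates T1 at 12 weeks after baseline, but by the Procedures timing the 12-week programme ends at week 15, so T1 needs one anchor for both arms

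*Protocol article*

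**What the plan says.** The protocol article describes the timing of T1 in several places.

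- **Procedures**, on the visit schedule: "Assessments will take place at baseline (T0), after twelve weeks of treatment (T1". The same paragraph adds: "T0 will be scheduled three weeks before the start of the treatment".
- **Lifestyle intervention**, on duration: "The lifestyle intervention consists of a 12-week program (see Table 1".
- **Primary outcome**, on KIDSCREEN-27: "Quality of life is assessed at T0 (Baseline), T1 (end of intervention), T2 (six months after baseline), and T3 (12 months after baseline". The Secondary outcomes and Lifestyle measurements sections use the same end-of-intervention label for T1.
- **Outcomes**, Table 2, footnote b: "T1 twelve weeks after baseline". Footnote a defines T0 as baseline; footnotes c and d count T2 and T3 from baseline too.
- **Background**, on the primary objective: "quantify the short-term (after 12 weeks) and long-term (after 6 and 12 months) effectiveness on quality of life". The 12-week assessment is thus the short-term part of the primary objective.
- **Care as usual**: a 1.5-hour parent session and an e-health module of about two hours for the child, followed by usual care. No 12-week programme is described for this arm.

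**The concern.** The Procedures text and the Table 2 footnote run on different clocks. One counts 12 weeks from the start of treatment, the other 12 weeks from baseline. They would agree only if treatment began at T0, and the article says that it begins three weeks later.

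Two things are at stake.

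1. If staff schedule from Table 2, the short-term quality-of-life comparison is made while intervention families are still in treatment. KIDSCREEN-27 has a one-week recall, so a rating at week 12 after T0 would describe the ninth treatment week and not the state after the programme. The same T1 label serves the CBCL, COTAPP, somatic and lifestyle outcomes.
2. If staff schedule from the treatment-based wording, the date is clear in the intervention arm but not under care as usual, where no programme ends at 12 weeks. The article shows no rule that ties the two arms to the same number of weeks from T0. In an unblinded trial with a parent-rated outcome, any difference in elapsed time would be mixed with the treatment effect.

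**Working it through.** **The plan's own figure.** The only computed figure in the article is the evaluable sample size of 66 (Sample size and power). It reproduces as the group-by-time interaction in a repeated-measures analysis of variance with 2 groups and 3 time points: f = 0.39, two-sided alpha 0.05, noncentrality N × f², degrees of freedom 2 and 2(N − 2). At N = 66 the power is 0.807. The calendar date of T1 does not enter this formula, so the sample size stands whichever date is meant.

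**Inputs for the timing check**

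| Input | Value | Source |
|---|---|---|
| Lead-in from T0 to start of treatment | 3 weeks | Procedures |
| Length of programme | 12 weeks | Lifestyle intervention |
| T1, treatment clock | after 12 treatment weeks | Procedures; same event in Primary outcome |
| T1, baseline clock | 12 weeks after T0 | Table 2, footnote b |

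**Step 1. End of treatment, counted from T0.** Lead-in + programme length = 3 + 12 = week 15.

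**Step 2. Treatment weeks completed at week 12 after T0.** 12 − 3 = 9.

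**Step 3. Share of the programme elapsed under the footnote.** 9 / 12 = 75%. Outstanding: 3 / 12 = 25%.

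**Step 4. Gap between the two definitions.** 15 − 12 = 3 weeks. In general the gap equals the lead-in, so it vanishes only if the lead-in is zero.

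**Step 5. Sessions affected.** Table 1 lists 12 on-site sessions. If they are given once a week and in table order, sessions 10 to 12 would still be due at week 12 after T0; session 11 is relapse prevention. This is an assumption, because the article treats the session order as a guideline and allows flexibility. The 25% in Step 3 is counted in weeks and does not depend on it.

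**Step 6. Which text is out of line?** Procedures, Primary outcome, Secondary outcomes and Lifestyle measurements all tie T1 to the end of treatment. Footnote b alone explicitly counts 12 weeks from baseline. The abstract's 12 weeks follows a T0 placed at study start but names no anchor, so it can be read either way.

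**The case against.** The strongest reply is that this is a drafting slip. The operational text and the outcome sections agree that T1 follows the intervention, and the contrary date sits in one footnote of a list that counts every visit from baseline. That stands, and it is why the footnote is treated here as the likely error rather than as the plan's real rule. It does not remove the contradiction: the footnote belongs to the table of assessment times, and nothing shown tells staff which date prevails.

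A second reply is that visit windows and control-arm scheduling belong in the full protocol, and that Figure 1, which shows the procedure, is not available here. This also stands as far as missing detail goes. The point made here is narrower: the article states two dates for one visit, and the text would need correcting even if the figure were clear.

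A reader might be tempted by four stronger readings, none of which the article supports.

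- **That less than a quarter of the programme would have been given at T1.** The reverse holds: about three quarters would have been given.
- **That T1 is the single primary time point.** The primary objective names 12 weeks, 6 months and 12 months, and the sample-size definition uses baseline, 12 weeks and 26 weeks.
- **That care-as-usual children are assessed at week 12 and intervention children at week 15.** This could happen, because care as usual has no 12-week programme, but no text says so. Procedures gives one schedule for the whole trial, and ongoing usual care could in principle be dated from a treatment start.
- **That the sample-size paragraph has the wrong date.** Its 12-week entry refers to the intervention and is compatible with T1 at the end of treatment.

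**Conclusion.** The contradiction is real and should be fixed. By the article's own 3-week lead-in and 12-week programme, the end of the intervention is 15 weeks after T0. Table 2 puts T1 at 12 weeks after T0, 3 weeks earlier, with the last quarter of the programme not yet given. This rests on the two stated durations being applied literally.

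The weight is moderate. The ambiguity touches the short-term part of the primary objective and every other outcome measured at T1. It leaves T2, T3 and the sample size as they are. The article does not establish that any child was or will be assessed before the programme ends, nor that the arms differ in timing; it permits both, and no bias can be quantified from what is shown.

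**What to change.** 1. Define T1 once, as weeks from T0, for both arms and with the same visit window. To match the end-of-intervention label used for the outcomes, that is 15 weeks after T0 by the stated 3 + 12. State explicitly that the same date applies under care as usual.
2. Correct footnote b of Table 2 accordingly, and make clear that the abstract's 12 weeks means 12 weeks of treatment.
3. For children already assessed, report the actual number of days from T0 to T1 by arm. Add a sensitivity analysis of the T1 comparison that includes this interval. If the intervals hardly overlap between arms, say so, because a model cannot then separate elapsed time from treatment.

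The cost is protocol wording, visit scheduling for children not yet at T1, and one small additional analysis. No extra visit or participant is needed. The article expected the N = 80 data collection to finish in spring 2024, so for many children step 3 may be the only part that can still be applied.
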